### Data analysis

The analysis will be done on an intention to treat basis. Those who have done less than six sessions will be considered withdrawals.

The descriptive analysis will be done in proportion to the quality variables and the average values for the quantities, with the corresponding measures of dispersion.

To observe the effect of the intervention in quality of life related to health, the change of habits and the costs derived from related resources, the T-Tests will be used for paired data and the McNemar Test or equivalents for quantitative or qualitative variables or their non parametric equivalents, if the distribution of the variable does not comply with the criteria of normality (Kolmogorov-Smirnof).

To analyze the factors that have influence over the changes of quality of life related to health (CVRS) and those related with the intervention, models of multiple regressions will be used. In each regression model the dependent variable will be derived from the calculation or the difference between ratings in the beginning of the study and the ratings at the end of the SF-36; the rest of the variables determined in the study will be included as independent variables. As the first step in the analysis of regression the adequate diagnosis will be done to detect extreme values and verify conditions of applicability (homocedastisity, normality and independence of waste). If needed the necessary transformations will be done in the dependent variables for the fulfillment of applicability conditions. The criteria of selection of variables for the estimation of multivariable models will be a Forward-Stepwise with the criteria of input of p < 0.05 and a criteria of output of p > 0.10.

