## Method/Design

Design: Cluster randomized trial, controlled and multicentric, comparing one group of patients that take part in the Health Workshops, with another group of similar characteristics that don't.

Setting: The study will be done in Heath Care Centers of Barcelona City.

Randomization unit: Primary care Teams (PCT)

Study Population: Population around the Centers that participate in the Study and that meet the criteria of inclusion.

Inclusion criteria:

• Persons of both sexes between 18 and 65 who consent to do so.

Exclusion criteria:

• If there is an objection to participating during a period of 12 months.

• If there a language difficulty, unable to understand or express in Spanish or Catalan.

• If there are acute mental problems.

• Other health problems which may be a difficulty in following the workshop, (like terminals, organic pathology...).

Sample size calculation: Accepting an Alfa risk of 0.05 and a Beta risk of 0.2 in a bilateral contrast, 108 individuals per group are needed in order to detect how statistically effective it is in a 20% difference between groups in quality of life with the SF-36 Questionnaire. We have estimated a 10% rate of loss in participation. The ARCOSENO approximation has been used.

Variables in the study: We collect socio-demographic variables from all participants: age, sex, studies, employment or work situation.

Principal Variable: HRQOL measured by means of SF-36 Questionnaire. We have selected the quality of life perceived indicator as the main variable as it is sensible to small changes [19].

Variables related to the intervention:

• Number of sessions the person has attended.

• IPAC Questionnaire for variables related to physical activity (the IPAC questionnaire has been used in research around this area so it allows us to compare the data obtained.)

• The variables related to eating habits will be collected by means of Questionnaire PREDIMED [15], which is validated and used in our area, as so allow us to compare results.

• Blood Pressure, Lipid Profile, Height, Weight, will be gathered from the computerized clinical history.

• To estimate the costs we will add the time spent by professionals directly related with the intervention (telephone calls, meetings with participants, gathering of data, workshops...)

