• Gathering of information: the gathering of data will be done in both groups, (intervention and control groups): before each intervention (Health Workshop), at the end of the intervention and in 6 months and 12 through self administered questionnaires in Teleform^© ^format.

Description of the Study (Figure 1)

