**Figure 1 F1:**
[figure not shown]
**Algorithm of the study**.

The stages of this study are the following:

Phase Recruitment and selection:

1 The recruitment of the PCT: The project is explained to professionals belonging to the Health Centre. Those interested in participating in the recruiting of patients will sign a commitment of participation in the Project. The participants will be recruited by these professionals and their inclusion will be consecutive. Once the recruitment has ended, the groups will be randomized in the intervention or control group. Persons interested will fill up an application form for the Workshop, which will be available in their Health Care Center (HCC) and where they have to give their name, phone number, and time availability.

The Blood Pressure (BP) and Weight data will be gathered (in those persons who consent), at an individual visit after the informative meeting. They will be asked to have a Lipid Profile (if it is not available in their clinical history in a 3 months period before the workshops begins), and again after 12 months.

Phase The Forming of the Study Groups

2 Based on the persons who have given their consent to participate, an random assignation to one or another group will take place, and the workshops will then start (with groups of 12 to 15 persons in each).

Phase Intervention (only in the group intervened)

3 The group intervention then starts in 8 sessions in which life activities will be approached in a progressive manner. During the sessions, tools will be offered to increase knowledge and develop abilities and motivations that help with life activities and the progressive incorporation of healthy habits. At the end of each session support material will be handed out with the session's contents and indications of activities to practice during the week.

The workshops will be offered at different schedules to facilitate assistance. The contents of the sessions are in Table 1.

**Table 1 T1:** Subject matter of the sessions in the work shop

Session	Content
1	Breathing. Tobacco, learning from experience.

2.	Eating and drinking adequately, a balanced diet.

3.	Elimination. The importance of regular disposal. Guides to avoid constipation. Hygiene. The importance of personal hygiene.

4.	Movement and maintaining adequate positions. Doing physical activity. Wearing adequate clothes.

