5.	Sleep and rest. Recommendations for a good rest and sleep. Leisure activities. The importance of dedication time to leisure.

6.	Avoid physical and emotional dangers. Self-esteem.

7.	Communication with others and social interaction. Managing one's emotions.

8.	Work and feel useful. The importance of activities that produce a sense of satisfaction.

Each session starts with a breathing exercise that helps participants to center themselves in the group. Next they share the week's experiences and clarify doubts. Followed by the theoretical content about the subject of the session and the practical exercises that to be done during the next week. The session ends with a space to clarify doubts and share reflections that have come up through the exposure of the theoretical concepts.

At the end of each session we hand out texts to be kept in their files and that will form, at the end of the Health Workshop, a MANUAL OF HEALTH CARE AND MAINTENANCE.

We have elaborated specific material, (with slides and points dealt with in the sessions) to ensure the unification of the message given. Also, we have elaborated support and reminder material for each session which gathers all the contents of the sessions. Such material is handed out at the end of each session to be kept in the files provided at the beginning of the Health Workshop, and which will, in the end, form a Manual for Health Self-Care and Maintenance.

The control group will continue to receive normal attention and will have the possibility, if they so desire, of doing the Health Workshops at the end of the Project, (if it has proven effective), once the 12 months are over with the last evaluation.

Phase Closing of the Project

4 Gathering and analyzing the last data and communicating the results.

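### Intention to treat is declared, but a six-session attendance rule that can apply only to the workshop arm classes low attenders as withdrawals; if that means exclusion, the comparison can be biased

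*Protocol article*

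**What the plan says.** The protocol article, Data analysis, opens with two adjacent sentences: "The analysis will be done on an intention to treat basis. Those who have done less than six sessions will be considered withdrawals".

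Other places bear on how the second sentence works:

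- Description of the Study, intervention phase. The heading is "Phase Intervention (only in the group intervened", and the text reads: "The group intervention then starts in 8 sessions in which life activities will be approached in a progressive manner". The threshold is therefore six of eight sessions, or 75% attendance, and only one arm has sessions to attend.
- Same section, on controls: "The control group will continue to receive normal attention". They may take the workshops only after the 12-month evaluation.
- Method/Design, variables related to the intervention: "Number of sessions the person has attended". Attendance is recorded, and it is known only after allocation.
- Method/Design, gathering of information: "the gathering of data will be done in both groups, (intervention and control groups", with time points before the workshop, at its end, and at 6 and 12 months. No attendance condition is attached.
- Method/Design, sample size: "We have estimated a 10% rate of loss in participation". The allowance does not say whether low attendance counts as loss.

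**The concern.** The first sentence fixes the analysis set by allocation. The second creates a category defined by how much of the intervention a person took up, and places it in the analysis section without saying what is done with it. In that position the usual meaning is that such people are not analysed, or not analysed as members of their arm.

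The rule is one-sided by construction. Applied literally to both arms, it would make every control a withdrawal, so it must be meant for the intervention arm only. If it removes people, the comparison becomes workshop attenders with at least six sessions against all controls, adherent or not. Randomisation does not protect that comparison. Completing six of eight weekly sessions plausibly goes with motivation and health, which also bear on self-reported quality of life, diet and physical activity.

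At stake is who enters the primary SF-36 comparison. Two analysts following the text in good faith could use different analysis sets, and a choice made after the data are seen would be hard to defend.

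**Working it through.** **1. The plan's own figure.** The article gives two-sided alpha 0.05, beta 0.2, a 20% difference, the arcsine approximation, 10% loss and 108 per group. It gives no base proportion; I assume 40% against 60%.

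- h = 2·asin(√0.6) − 2·asin(√0.4) = 0.403
- n = 2(1.960 + 0.842)² / 0.403² = 96.8, so 97 evaluable per group
- 97 / 0.9 = 107.8, so 108

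The stated size reproduces. The 97 evaluable per arm also sets the scale: the detectable standardised difference is (1.960 + 0.842)·√(2/97) = 0.40.

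**2. Size of the bias if low attenders are excluded.** Let w be the share of the intervention arm with fewer than six sessions, and g the amount, in SD, by which attenders' mean outcome exceeds low attenders'. If attenders have mean a, the whole arm has mean a − w·g. Dropping low attenders therefore shifts the arm's mean, and the estimated effect, by

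bias = w·g.

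**3. Inputs for w and g.** Neither is in the article; both are assumptions. For w, I take 10% to 25%. The lower end equals the article's allowance for loss in participation, the only related rate it gives. For g, I take 0.3 to 0.5 SD.

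**4. False-positive rate with no true effect.** With 97 controls and 97(1 − w) intervention participants, SE = √(1/[97(1 − w)] + 1/97) in SD units, and d = bias/SE. The two-sided rejection rate is Φ(d − 1.96) + Φ(−d − 1.96).

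| w | g (SD) | Intervention n | SE | Bias (SD) | Bias / 0.40 | Type I error |
|---|---|---|---|---|---|---|
| 10% | 0.3 | 87.3 | 0.148 | 0.030 | 7.5% | 5.5% |
| 10% | 0.5 | 87.3 | 0.148 | 0.050 | 12.5% | 6.3% |
| 25% | 0.3 | 72.75 | 0.155 | 0.075 | 19% | 7.7% |
| 25% | 0.5 | 72.75 | 0.155 | 0.125 | 31% | 12.7% |
| any | 0 | – | – | 0 | 0 | 5% |

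The table removes low attenders on top of the 10% loss. If the 10% already covers some of them, more remain in the analysis; the bias w·g is unchanged, and the error rates move little. With w = 25%, g = 0.5 and 108 × 0.75 = 81 analysed, the rate is 13.2%.

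**5. Cross-check on the proportion scale.** Suppose a 40% response in both arms, 10-40% of the intervention arm removed, and a response gap of 5-20 percentage points. The spurious difference runs from 0.10 × 5 = 0.5 points to 0.40 × 20 = 8 points, and the type I error from 5.1% to 16.3%.

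**6. Power lost through removal alone.** With 40% against 60% and 97 controls, removing 10/20/30/40% of the 97 leaves 87/78/68/58. Power is then 77.9/75.4/72.1/67.9%, against 80.1% with no removal.

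Steps 1 to 6 treat individuals as independent. Method/Design describes a cluster randomised trial, so the rates illustrate the mechanism and are not the operating characteristics of that design.

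**The case against.** The strongest reply is that exclusion is nowhere stated. The only explicit statement about the analysis set is intention to treat. The second sentence can be read as a definition of workshop non-completion, useful for reporting alongside the recorded number of sessions. The data-collection plan supports this: questionnaires go to both groups at every time point with no attendance condition, and the 12-month lipid profile is also unconditional. The English in this section is loose, so one word should not carry too much. This stands in part. A reader might infer that the plan certainly discards low attenders and that the trial is therefore biased; the article does not support that. If low attenders are followed and analysed as allocated, intention to treat is intact and the rule is only a label.

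A second reply concerns direction. Bias toward the workshops requires low attenders to do worse. The regression outcome is the change in SF-36 between the start and the end of the study, and nothing in the article says how low attenders change. Healthier or working people might attend less. So the direction is plausible, not established.

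A third concerns size. A reader might take a false-positive rate of 8-13% as the cost. That range needs about a quarter of the arm to be low attenders, a rate not in the article. At 10% the same formulas give about 5.5-6.3%.

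What the replies do not remove is the ambiguity. The article never says that these withdrawals stay in the analysis, and the harmful reading is the more natural one in that place.

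**Conclusion.** The concern holds as a conditional one. A declared intention-to-treat analysis is followed at once by a one-sided rule based on post-allocation attendance, with no statement of what the rule does. If it means exclusion, it contradicts intention to treat and biases the comparison by the share excluded times the outcome gap. With 10-25% low attenders and a gap of 0.3-0.5 SD, both assumed, the bias is 0.03-0.125 SD, or 7.5-31% of the 0.40 SD the trial can detect. The type I error is then about 5.5-13%, ignoring clustering. With no gap there is no bias; if low attenders are kept as allocated, the problem is one of wording only.

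It should be corrected before analysis. The rule bears on who enters the primary comparison, and this is more than an omitted detail: an analysis plan that followed the sentence as written would inherit the conflict.

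**What to change.** Replace the second sentence with: *All participants are analysed in the arm to which they were allocated, whatever their attendance; withdrawal means withdrawn consent or loss to follow-up.* The wording refers to the allocated arm and not to the arm of the primary care team. Method/Design names the team as the randomisation unit, while the description of the study groups speaks of random assignment based on the persons who consented.

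Confirm that the follow-up already planned for both groups also covers those with fewer than six sessions. Use six or more sessions only to describe adherence, or to define a secondary per-protocol or complier-average analysis that is labelled as such.

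The cost is one sentence, plus making sure that planned questionnaires and 12-month measures reach low attenders. The sample size stays at 108 per group. The downside is that the primary estimate, which then includes people who took up little of the workshop, may be slightly smaller.

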**Methods/Design:**

Controlled and random clinical testing, comparing a group of persons who have participated in the Health Workshops with a control group of similar characteristics who have not participated in the Health Workshops.

Field of study: the research is being done in Health Centers of the city of Barcelona, Spain.

Population studied: The group is composed of 108 persons that are actually doing the Health Workshops, and 108 that are not and form the control group. They are assigned at random to one group or the other.

Data Analysis: With Student's t-distribution test to compare the differences between numerical variables or their non parametric equivalent if the variable does not comply with the criteria of normality. (Kolmogorov-Smirnof test). Chi-square test to compare the differences between categorical variables and the Logistic Regression Model to analyze different meaningful variables by dichotomous analysis related to the intervention.

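### The Data analysis section tests the workshop effect with before-after paired tests and fixes no between-arm contrast for the SF-36, in conflict with the Abstract, the controlled design and the sample size

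*Protocol article*

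**What the plan says.** The protocol article's Data analysis section states the purpose as "To observe the effect of the intervention in quality of life related to health, the change of habits and the costs derived from related resources" and then names the tools: "the T-Tests will be used for paired data and the McNemar Test or equivalents for quantitative or qualitative variables", with non-parametric equivalents if normality fails. Quality of life measured by the SF-36 is the principal variable, so this sentence governs the primary objective.

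The same section then describes multiple regression to study factors that influence change in quality of life and factors related to the intervention. There, "the dependent variable will be derived from the calculation or the difference between ratings in the beginning of the study" and the end-of-study ratings. All other study variables are candidates, chosen by forward stepwise selection (entry at p < 0.05, removal at p > 0.10). Allocated arm is not named.

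The Abstract (Methods/Design) gives a different set of tests: "With Student's t-distribution test to compare the differences between numerical variables or their non parametric equivalent", then "Chi-square test to compare the differences between categorical variables", then logistic regression. These follow a description of workshop participants compared with a control group.

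The Method/Design section calls the study a "Cluster randomized trial, controlled and multicentric, comparing one group of patients that take part in the Health Workshops, with another group". The sample size is set for a 20% difference between groups.

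**The concern.** A paired t-test or a McNemar test uses two measurements on the same person. No matching of persons across arms is described anywhere, so pairing here can only mean before versus after. Such a test asks whether people changed, not whether workshop participants changed more than controls.

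The distinction matters in this trial. Participants are volunteers who apply for a workshop, and they complete self-administered questionnaires before the workshop, at its end, and at 6 and 12 months. Regression to the mean, season and repeated questionnaires can move the scores in both arms. The control arm exists to remove that shared movement, and a within-arm test instead credits it to the workshop. The result also has a consequence within the study: controls are to be offered the workshop afterwards if it has proven effective.

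**Working it through.** **1. What the sample size was built for.** Inputs from the Method/Design section: two-sided alpha 0.05, beta 0.2, a 20% difference between groups, arcsine approximation, 10% loss, 108 per group. The base proportions are not given. I assume 40% versus 60%, the least favourable pair.

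- n = 2(z₀.₉₇₅ + z₀.₈₀)² / h², with h = 2·asin(√0.6) − 2·asin(√0.4) = 0.403
- n = 2 × (1.960 + 0.842)² / 0.403² = 96.8, so 97 per group
- with 10% loss: 97 / 0.9 = 107.8, so 108

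The plan's 108 is reproduced. Other assumed pairs give 107 (45% v 65%), 104 (50% v 70%) and 90 (20% v 40%). The stated figure is therefore consistent with a comparison of two independent groups, a contrast that the paired tests do not make.

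**2. The places side by side.**

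| Place | Comparison described |
|---|---|
| Method/Design, Design | Intervention versus control |
| Method/Design, Sample size calculation | Difference between groups |
| Abstract, Methods/Design | Student's t, chi-square and logistic regression, after a comparison with a control group is described |
| Data analysis, effect of the intervention | Paired t-test and McNemar: before versus after |
| Data analysis, regression | SF-36 change; arm not named, stepwise selection |

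**3. What the paired test does when the workshop has no effect.** Assumptions: 97 analysed per arm (108 × 0.9 = 97.2), normal change scores, the same mean shift d in both arms in SDs of the change score, and no clustering. The documents give no figure for d, so a range is shown. The paired t statistic has 96 degrees of freedom and non-centrality d × √97 = 9.85d. The probability of p < 0.05 follows from the non-central t distribution.

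| Shared shift d | Non-centrality | Paired test in intervention arm significant | Two-sample t-test of change significant |
|---|---|---|---|
| 0 | 0 | 5% | 5% |
| 0.1 | 0.98 | 16% | 5% |
| 0.2 | 1.97 | 50% | 5% |
| 0.3 | 2.95 | 83% | 5% |

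The last column stays at 5% because a shared shift cancels in the difference between arms. A simulation of 20,000 trials agrees. At d = 0.2 the paired test rejected in 49.8% and the two-sample test in 4.8%. At d = 0.3 the figures were 83.6% and 4.9%.

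**4. What baseline adjustment would add.** Let r be the correlation between baseline and follow-up, with equal variances. In units of the outcome variance, a raw change score has variance 2(1 − r), and follow-up adjusted for baseline has 1 − r². The ratio is (1 + r)/2, so the reduction is (1 − r)/2: 25% at r = 0.5, 20% at r = 0.6 and 15% at r = 0.7. The values of r are assumed.

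**The case against.** A reader might infer that the plan never compares intervention with control. The documents do not support that. The Abstract's Student's t and chi-square tests read most naturally as between-group tests. The regression in the Data analysis section admits all other study variables, data are gathered in both arms, and part of its stated aim concerns the intervention. Arm could therefore be a candidate, and its coefficient in a change-score model would be a between-arm comparison. What remains is that arm is not named and that stepwise selection may drop it, in which case the model gives no estimate of the workshop effect. The two accounts of the analysis also still disagree.

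A reader might also take the raw change score, or the absence of baseline SF-36 from the named covariates, as an error. It is not one. Under randomization a between-arm comparison of change is valid, baseline may be among the remaining variables, and an article need not list every covariate. Adjustment is a gain in precision.

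Third, the size of the problem depends on the assumed drift. With none, the paired test keeps its 5% level. This is fair, and it is why a range is given. Nor do the documents say that efficacy would be concluded from a significant change in one arm and a non-significant one in the other, so no error rate for that rule is claimed here.

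Finally, an analysis plan that is not shown may say more. That would not cure a test named wrongly for the primary outcome in the published protocol.

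**Conclusion.** The point stands in this form. As written, the Data analysis section assigns within-person tests to the effect of the intervention on the primary outcome and on habits, and it fixes no between-arm contrast. It conflicts with the Abstract, with the controlled design and with a sample size set for a between-group difference.

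The consequence can be large. With no workshop effect, the chance of a significant intervention-arm result goes from 5% with no shared drift to 83% with a drift of 0.3 SD of the change score. A between-arm test stays at about 5%. These figures assume 97 analysed per arm, equal drift in both arms and no clustering. The drift values are illustrative, but the direction of the problem does not depend on them: any shared change is attributed to the workshop.

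**What to change.** Reconcile the Abstract with the Data analysis section and pre-specify one between-arm efficacy analysis:

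- Regress follow-up SF-36 on allocated arm, forced into the model and outside any stepwise selection, with baseline SF-36 as a covariate.
- Allow for the primary care team, which Method/Design names as the randomization unit.
- Report the adjusted difference between arms with its 95% confidence interval.
- State the timepoint. Data are collected at the end of the intervention, at 6 months and at 12 months, and the Data analysis section refers only to the end. The sponsor must confirm which is primary.
- Use analogous models for the secondary outcomes: linear for numerical variables, logistic for dichotomous ones.
- Keep paired t-tests and McNemar tests only as within-arm description, and keep the stepwise regression as exploratory.

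The cost is small but not nil. No new data or participants are needed, since baseline and follow-up SF-36 are already collected in both arms. Allowing for clustering will widen the confidence interval. By how much cannot be worked out here, because neither the number of teams nor an intracluster correlation is given.

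### No stated analysis of the SF-36 effect guarantees adjustment for the baseline SF-36 score, so precision is given up and chance baseline imbalance can stay in the estimate

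*Protocol article*

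**What the plan says.** SF-36 quality of life is the principal variable, and it is measured in both arms before the workshops, at their end, and at 6 and 12 months (Method/Design). Three statements bear on how the arms will be compared on it:

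- **Data analysis, effect of the intervention:** t-tests for paired data, McNemar's test, or non-parametric equivalents. No baseline covariate is named.
- **Abstract, Methods/Design:** Student's t-test or its non-parametric equivalent. Again no baseline covariate.
- **Data analysis, factors that influence change:** multiple regression. In each model "the dependent variable will be derived from the calculation or the difference between ratings in the beginning of the study" and those at the end. The remaining study variables serve as independent variables, and "The criteria of selection of variables for the estimation of multivariable models will be a Forward-Stepwise" procedure, with entry at p < 0.05 and removal at p > 0.10. No term is exempt from selection.

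The sample size rests on "Accepting an Alfa risk of 0.05 and a Beta risk of 0.2 in a bilateral contrast, 108 individuals per group are needed" to detect an effect described as "in a 20% difference between groups in quality of life with the SF-36 Questionnaire". The article adds "We have estimated a 10% rate of loss in participation".

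**The concern.** Taking the difference from baseline is not the same as adjusting for baseline. An unadjusted change score fixes the slope of follow-up on baseline at 1. Where the scores have equal SDs and correlate below 1, the true slope is below 1, and two things follow. The comparison is noisier than it needs to be. It also over-corrects whatever baseline difference chance has produced, because the arm that starts higher tends to regress further.

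The article commits itself on both the form of the regression outcome and the selection rule, so this is a stated choice and not a detail left for an analysis plan. Under that rule the trial arm itself can also be dropped from the model. At stake is the precision of the principal comparison, and how well it stands up if the arms happen to differ at the start.

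**Working it through.** **Inputs.** From Method/Design: two-sided alpha 0.05, power 0.80, 108 per group, 10% loss. Not in the article and therefore assumed: the correlation r between baseline and follow-up SF-36 (shown for 0.5 to 0.7, with wider values where useful), equal SDs at both times, and no clustering.

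**The plan's own figure.** The article says "The ARCOSENO approximation has been used" but gives no base proportion. Assuming 40% against 60%:
- h = 2·asin(√0.6) − 2·asin(√0.4) = 0.403
- n = 2·(2.802/0.403)² = 96.8, so 97 per group
- 97/0.9 = 107.8, so 108

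The stated size is reproduced, with 97 evaluable per arm. Nothing below changes it.

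**Precision.** Per person, in units of SD²:
- change score: 2(1 − r)
- baseline-adjusted: 1 − r²
- ratio: (1 − r²)/[2(1 − r)] = (1 + r)/2

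The standard error of the difference is √(2·variance/97). If the change score has 80% power, adjusted power is Φ(2.802/√((1+r)/2) − 1.96).

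| r | Variance ratio | SE, change (SD) | SE, adjusted (SD) | Adjusted power when change has 80% | n per arm, adjusted, matching 97 with change |
|---|---|---|---|---|---|
| 0.5 | 0.75 | 0.144 | 0.124 | 89.9% | 73 |
| 0.6 | 0.80 | 0.128 | 0.115 | 87.9% | 78 |
| 0.7 | 0.85 | 0.111 | 0.103 | 86.0% | 83 |

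Over a wider range the ratio runs from 0.65 at r = 0.3 to 0.95 at r = 0.9.

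**Chance imbalance.** Given a baseline difference D in favour of one arm, the unadjusted change score shifts by −(1 − r)D for that arm. For D = 0.2 SD this is 0.10, 0.08 and 0.06 SD at r = 0.5, 0.6 and 0.7. Under individual randomisation with 97 per arm, the SD of D is √(2/97) = 0.144, so 0.2 SD is not unusual.

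**Simulation** (individual randomisation, 97 per arm, 8,000 trials for each r) gave variance ratios of 0.76, 0.81 and 0.85. The change-score estimate had slopes on the imbalance of −0.49, −0.39 and about −0.30. The adjusted estimate had slopes near 0.

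**Would stepwise selection rescue the regression?** If baseline SF-36 is a candidate, its correlation with the change is −√((1 − r)/2): −0.50, −0.45 and −0.39 at r = 0.5, 0.6 and 0.7. With 194 people and considered alone, its chance of entering at p < 0.05 is Φ(atanh(√((1−r)/2))·√191 − 1.96). That exceeds 0.99 for r up to 0.8 and is 0.88 at r = 0.9.

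**The case against.** The strongest reply is that the regression is not the test of the effect. The Data analysis section gives the effect to paired tests and introduces the regression as a search for influencing factors. That is right, and it moves the weight of the point: the precision and imbalance figures apply mainly to the t-tests, which have no baseline term at all.

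Second, the remaining study variables may include baseline SF-36, in which case stepwise selection would nearly always pick it up. This also stands as far as it goes. On that reading most of the loss disappears from the regression. But the phrase is ambiguous, since the baseline score is already used to form the outcome, and on neither reading is the term forced. The t-tests are untouched by it.

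Third, a change score is unbiased on average under randomisation. True: the point concerns precision and bias conditional on the imbalance that occurred.

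Some stronger readings are tempting but unsupported:
- A reader might infer that the trial is underpowered because of this. The article contains no baseline-adjusted calculation to fall short of, and its sample size is not wrong on this ground. Adjustment is an available gain.
- A reader might put a figure on the imbalance from randomising few primary care teams. The article gives neither the number of teams nor an intracluster correlation. It also describes random assignment of persons in some places and of teams in another. The shift from a between-team imbalance would depend on how stable team means are, which the individual-level r does not describe.
- A reader might infer that modelling change is itself the fault. Once baseline is in a linear model, follow-up and change give the same arm coefficient and standard error.

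**Conclusion.** The point holds as a matter of efficiency and conditional bias. None of the stated analyses secures baseline adjustment of the principal outcome: the t-tests have no such term, and the stepwise regression leaves both baseline and arm to a p-value. Against an unadjusted change-score comparison, adjustment removes 15% to 25% of the variance for r between 0.7 and 0.5, and protects against a shift of about (1 − r)D from a chance imbalance D. These sizes rest on an assumed r, equal SDs and no clustering. No figure in the article is invalidated. It is a moderate weakness that should be put right, not one that makes the planned comparison invalid.

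**What to change.** Prespecify the between-arm SF-36 comparison as a linear model of the follow-up score (or, equivalently, its change) with:
- arm and baseline SF-36 always included and exempt from selection;
- primary care team accounted for, with a small-sample correction if teams are few;
- the adjusted mean difference reported with its 95% confidence interval.

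Keep forward-stepwise selection for the exploratory models of influencing factors only. Checks of the residuals remain appropriate, since the change of model does not remove the need for them.

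The cost is wording in the analysis section. The baseline score is already collected in both arms, so no new data are needed and the sample size stays as it is.
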